**Asthma Control Test (ACT) Surveys & IAQ Measurements (No. of measurements = 24)**							
Statistical Power	0.82	0.83	0.90	0.89	0.90	0.98	0.92
Sample Size Per Group	19	9	6	4	3	3	2
Total Sample Size	76	36	24	16	12	12	8
Total Sample Size (adjusted for 10% dropout)	**84**	40	26	**18**	13	13	**9**
**Pulmonary Function Testing (No. of measurements = 4)**							
Statistical Power	0.8	0.81	0.8	0.83	0.86	0.83	0.82
Sample Size Per Group	50	23	13	9	7	5	4
Total Sample Size	200	92	52	36	28	20	16
Total Sample Size (adjusted for 10% dropout)	**220**	101	57	**40**	31	22	**18**
**Mold Measurements (No. of measurements = 2, baseline & end-line)**							
Statistical Power	0.81	0.81	0.82	0.8	0.82	0.83	0.86
Sample Size Per Group	70	32	19	12	9	7	6
Total Sample Size	280	128	76	48	36	28	24
Total Sample Size (adjusted for 10% dropout)	**308**	141	84	**53**	40	31	**26**

Sample sizes were calculated based on repeated measures ANOVA (α = 0.05, power = 0.80) and expected effect sizes, with adjustment for a 10% dropout rate.

### Data management and statistical analysis plan

The full data collection will include three categories of data: (1) human subject data, including demographic and socioeconomic characteristics and asthma-related health outcomes collected via baseline and follow-up questionnaires; (2) housing characteristics, including building and dwelling information; and (3) environmental exposure data, including indoor and outdoor air quality and mold measurements. All data will be de-identified prior to analysis to protect participant confidentiality, with direct identifiers removed before sharing. Data will be stored as comma-separated text files and spreadsheet files on a secure central server in the PI’s laboratory and processed electronically using Stata or Python in appropriate analysis formats. De-identified data will be shared only with the PI. Missing data will be handled using multiple imputation under the missing-at-random assumption, where collected data will be used to predict missing values. At least 20 imputed datasets will be generated, and convergence diagnostics and comparisons between observed and imputed data will be performed to assess plausibility [51]. Mixed-effects models for repeated measures will be used to account for within-subject correlations, and sensitivity analyses will compare complete-case and multiple imputation results.

Descriptive statistics will summarize participant demographics (e.g., age, sex, race/ethnicity, household income) and study variables by group, with continuous variables presented as means, medians, standard deviations, interquartile ranges (IQRs), or other distributional parameters, and categorical variables as frequencies and percentages. Appropriate statistical tests will be applied based on data type and distribution, including paired and unpaired t-tests, Wilcoxon signed-rank or rank-sum tests, and chi-square tests for categorical comparisons.

The primary analyses will follow the intention-to-treat (ITT) principle, including all randomized households analyzed according to their assigned intervention group, to evaluate the effects of ERVs and portable HEPA air cleaners on IAQ, mold reduction, and asthma-related health outcomes by comparing the intervention and control (sham) groups using repeated measures analysis of variance (ANOVA) with a within-between interaction. Pairwise comparisons will be conducted between each intervention and control group (Group 1 vs. Group 2, Group 3 vs. Group 4) and between intervention groups (Group 1 vs. Group 3), using Tukey’s Honest Significant Difference (HSD) test to adjust for multiple comparisons. Repeated monthly ACT scores will be analyzed using multivariate mixed-effects models to account for within-subject correlations over time. Per-protocol (PP) analyses will be conducted as sensitivity analyses and will include only households that adequately adhered to the assigned intervention protocol. Intervention adherence will be assessed using plug load logger data for both ERV and air cleaner units, including device operation status and operating duration [52]. Additionally, subgroup analyses will be conducted to explore whether intervention effects differ by demographic and socioeconomic characteristics, baseline asthma severity, and baseline IAQ.

For secondary analyses, multivariate linear and logistic regression models will examine associations among housing characteristics, occupant behaviors, indoor environmental exposures (e.g., air pollutants and mold), and asthma-related health outcomes. Housing characteristics will be considered as potential covariates or confounders, when applicable, based on biological plausibility and statistical considerations. Prior to multivariable modeling, correlations among environmental exposure variables (e.g., PM, NO_2_, VOCs, and mold indices) will be evaluated using Pearson or Spearman correlation coefficients, depending on data distribution. Variance inflation factors (VIFs) will also be calculated to assess multicollinearity among predictors. Highly correlated exposures will not be included simultaneously in the same model to minimize multicollinearity, overfitting, and unstable estimates.

Lastly, indoor and outdoor air quality data collected by low-cost sensors deployed throughout the study will be validated and calibrated against co-located research-grade monitors. Paired measurements from low-cost sensors and reference instruments will be used to develop calibration models. Linear regression will be used to estimate calibration coefficients, including slope and intercept, which will be applied to adjust low-cost sensor measurements for sensor bias and drift over time. Sensor performance will be assessed through quality assurance checks, including evaluation of data completeness, abnormal readings, and consistency with reference measurements. The calibrated data will subsequently be used in all analyses described above to ensure accuracy and consistency. All analyses will be conducted in Stata (v.19) [35] and/or R (v.4.5.2) [53] by multiple team members to minimize bias. Detailed procedures for sensor calibration and validation, including co-location with research-grade instruments and development of calibration models, are described in our previous calibration report [18].

The trial does not involve a Data Monitoring Committee (DMC) as the interventions (i.e., ERV and PAC) are non-pharmacological environmental interventions with minimal expected risk. Study oversight will be conducted by the PIs, who will monitor study progress, data quality, and participant safety throughout the trial. Any unexpected problems or adverse events, if they occur, will be documented and reported to the IRB in accordance with institutional requirements. The statistical analysis plan will be finalized prior to the final data lock and database unblinding. Any deviations from the prespecified analysis plan will be documented and reported transparently.

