### Study design

The AIRVAC study is a single-blind, placebo-controlled, four-arm, parallel-group, randomized controlled trial ERVs and portable HEPA air cleaners, with a pre-intervention period of up to 1 year and a 1-year post-intervention period. The pre-intervention period was designed to characterize baseline variability in indoor environmental conditions and health outcomes across seasons and to account for seasonal variations in longitudinal analyses using time-related covariates. Participants will be randomly assigned to one of four groups: (1) active ERV, (2) sham (placebo) ERV, (3) active portable HEPA air cleaner, or (4) sham (placebo) portable HEPA air cleaner.

The study involves five home visits. During the initial home visit (V0), the field team, which includes a BPI Building Analyst Professional (BAP)-certified investigator [34] and a licensed HVAC contractor, will conduct initial home visits (V0) to obtain information on housing conditions, health and safety concerns, and potential asthma triggers that may contribute to exacerbations or affect ERV installation. Key parameters to be assessed include home size, construction type, heating, ventilation, and air conditioning (HVAC) system, window operation, kitchen stove and hood, occupant behaviors, and other environmental risk indicators (e.g., visible mold, water damage, asbestos, chipping paint, pests, and pets). Additionally, for homes deemed eligible following the health and safety evaluation, blower door tests will be performed to measure the airtightness of the building envelope.

Following the initial visit, four follow-up visits (V1-V4) will be conducted to assess environmental exposures and health outcomes (two during the pre-intervention period and two during the post-intervention period). Fig 1 shows an overview of the study visit timeline with tasks that will be performed at each visit.

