### Participant recruitment

The target study population includes children aged 5–17 years and adults aged 18 years and older with asthma from 80 households. Initially, approximately 88 households will be recruited to account for potential dropout and ensure that the required sample size is maintained throughout the study period. Participants will be primarily recruited from applicants to Rebuilding Together North Texas (RTNTX), a nonprofit organization that administers the Safe & Healthy Homes program. This program provides essential home repairs, safety improvements, and accessibility modifications for low-income residents across diverse communities in the DFW area.

Eligibility requirements for participation in the study include: (1) homes must have at least one occupant with self-reported physician-diagnosed asthma; (2) homes must be non-smoking; (3) homes must be owner-occupied; and (4) participants must agree to participate in the entire 2-year study duration and allow for five home visits by the research team. Potentially eligible participants will complete an electronic screening form prior to enrollment, based on the inclusion and exclusion criteria listed below.

The inclusion criteria:

Age: children 5–17 years; adults ≥18 years.Individuals with physician-diagnosed asthma.Residency in the DFW area.English speaking and writing.Able to provide consent.Able to communicate regularly by phone.

The exclusion criteria:

Homes with any current smokersAnticipated relocation outside the DFW area within the two-year study period.Hazardous conditions and/or safety concerns in or around the participant’s home.Use of any device not provided as part of the study, including ERVs or portable HEPA air cleaners, in the participant’s home at any time during the trial.

Participant engagement will be maintained through home visits and monthly asthma surveys via phone. Primary participants will receive a total of $200 in gift cards across the four follow-up visits (V1-V4), and additional eligible family members may receive $100 each. Participants will have the option to keep the intervention device; those assigned to a sham device will receive an active device at study completion. Participants who do not complete required assessments will not be randomized or remain in the study. Compensation is contingent upon completing all study procedures, and participants who withdraw or fail to complete visits will forfeit subsequent payments.

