### Health outcome assessments

#### Primary outcome measures.

We will use the following measures to assess asthma control:

Asthma Control Test (ACT): Monthly ACT surveys will be administered electronically using an online survey link distributed to participants. The ACT is a 5-item, clinically validated questionnaire designed to assess the multi-dimensional nature of asthma control, including asthma symptoms, use of rescue medications, and the impact of asthma on daily functioning [38]. ACT scores range from 5 (“poor control of asthma”) to 25 (“complete control of asthma”), with a cut-off of 19 used to identify participants with suboptimal asthma control according to the Global Initiative for Asthma (GINA) guidelines: a score >19 indicates “well-controlled asthma,” whereas a score ≤19 indicates “poorly controlled asthma” [39,40]. Children under 12 years of age will complete the Childhood Asthma Control Test (C-ACT).Asthma Control Questionnaire (ACQ): In addition to monthly ACT, we will administer the ACQ during the home visits (V1-V4) to assess asthma control more comprehensively. The ACQ consists of 7 items covering asthma symptoms, rescue bronchodilator use, and lung function (FEV_1_, forced expiratory volume in one second, FEV_1_). Each scored on a 7-point scale from 0 (“no impairment”) to 6 (“maximum impairment”), and the overall score is calculated as the mean of all items, with lower scores indicating better control. Consistent with established guidelines, an ACQ score ≤0.75 will be used to identify “well-controlled asthma,” whereas a score ≥1.50 will indicate “poorly controlled asthma,” with intermediate values reflecting partially controlled asthma [41,42].

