### Power calculations

The sample size and statistical power for this 4-arm parallel-group randomized controlled trial is analyzed for various scenarios based on a range of likely magnitudes of outcomes for asthma-related health outcome and environmental exposure assessments (Table 1). Calculations are made utilizing a robust statistical software tool, G*Power ver. 3.1.9.7, for a repeated measures ANOVA with a within-between interaction [49]. A range of effect sizes from small (Cohen’s f = 0.10), medium (f = 0.25), to large (f = 0.40) are considered to accommodate varying expected intervention effects, ensuring both robustness and generalizability of the findings [50]. Sample size calculations were conducted for the health outcomes (ACT and PFT) and environmental outcomes (IAQ and mold measurements). Required sample sizes were estimated based on expected effect sizes to achieve a statistical power >0.80 and adjusted for a 10% dropout rate. For monthly ACT surveys (n = 24) and monthly average low-cost IAQ measurements (n = 24), the required sample sizes ranged from 84 households for a small effect size (0.10) to 9 households for a large effect size (0.40). For PFT and mold measurements, the required sample sizes were estimated at 220 and 308 households, respectively, for detecting a small effect size (0.10); 40 and 53 households, respectively, for a medium effect size (0.25); and 18 and 26 households, respectively, for a large effect size (0.40). Although larger sample sizes were required to detect a small effect size (0.1) for PFT and mold, these estimates represent the sample sizes needed to detect very small changes. Further, the AIRVAC study was primarily designed to evaluate intervention effects on asthma outcomes and IAQ, for which the estimated sample sizes were within the planned recruitment range. Therefore, the final target sample size was set at 80 households, with an initial recruitment target of 88 households to account for potential dropout.

**Table 1 pone.0358221.t001:** Sample size calculations.

Effect Size (Cohen’s f for ANOVA)	Small			Medium			Large
	0.1	0.15	0.2	0.25	0.3	0.35	0.4

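### The one missing-data sensitivity analysis the article states, complete-case versus multiple imputation, cannot detect withdrawal that depends on unobserved asthma outcomes

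*Protocol article*

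**What the plan says.** All from the Protocol article.

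- **Primary handling** (Data management and statistical analysis plan): "Missing data will be handled using multiple imputation under the missing-at-random assumption", with at least 20 imputed datasets.
- **Stated missing-data sensitivity analysis** (same section): "sensitivity analyses will compare complete-case and multiple imputation results". Complete case is not defined.
- **Other imputation checks** (same section): "convergence diagnostics and comparisons between observed and imputed data will be performed to assess plausibility".
- **Other sensitivity analysis** (same section): "Per-protocol (PP) analyses will be conducted as sensitivity analyses". This set is defined by device adherence from plug-load loggers, not by missing data.
- **Analysis set** (same section): intention to treat, with every randomised household in its assigned arm. Monthly ACT scores go into mixed-effects models.
- **Data collection** (Primary outcome measures): "Monthly ACT surveys will be administered electronically using an online survey link distributed to participants".
- **Attrition** (Participant recruitment): those who do not complete required assessments are not kept in the study, and "participants who withdraw or fail to complete visits will forfeit subsequent payments". Whether a monthly survey counts as a required assessment is not said.
- **Duration** (Study design): "with a pre-intervention period of up to 1 year and a 1-year post-intervention period". The Power calculations section counts 24 monthly surveys, which is therefore the maximum.

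**The concern.** An intention-to-treat result on all randomised households depends, for leavers, on what is assumed about the scores they never gave. Here that assumption is MAR. The outcome is self-reported every month for up to two years, and stopping because the device seems to bring no benefit is a plausible, outcome-related reason to leave. Removing people who miss required assessments can turn a gap into a permanent unobserved tail.

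A sensitivity analysis for missing data should ask how far the active-versus-sham conclusion depends on that assumption. The stated comparison asks something else. The two results may agree because both share the same blind spot. They may also differ because complete-case analysis is the more fragile of the two. In neither case does the reader learn whether the effect on asthma control survives if leavers did worse than imputed. With 80 households in four arms, about 20 per arm if evenly split, a few such leavers can move an arm mean.

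**Working it through.** **1. The plan's own figure.** Table 1, ACT row, f = 0.10, 24 measurements: power 0.82 with 76 households, 84 after 10% dropout. For the within-between interaction with k = 4 arms and m = 24, assuming correlation 0.5 and sphericity (the article gives neither):

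- λ = f²Nm/(1 − ρ) = 0.01 × 76 × 24 / 0.5 = 36.48
- df1 = 3 × 23 = 69; df2 = 72 × 23 = 1656
- power = 0.815, which matches the stated 0.82
- 76 × 1.1 = 83.6, so 84, as stated

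The sample size is not in dispute.

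**2. Which stated checks probe MAR?**

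| Stated check | What it examines | Probes departures from MAR? |
|---|---|---|
| Convergence; observed versus imputed | Behaviour of the imputation model | No |
| Per-protocol | Device adherence | No |
| Complete-case versus imputation, if complete case means every survey present | A stronger assumption against MAR | No |
| Same, if it means a mixed model on observed months | MAR against MAR | No |

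**3. Can the comparison mislead?** A large simulation used a baseline and one outcome, SD 1, correlation 0.5, true difference 0. Dropout was 10% in one arm and 20% in the other, with log-odds rising by 1 per SD of worse driving variable. Missing outcomes were imputed by regression on baseline within arm. All inputs are assumed.

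| Dropout driven by | Complete-case bias (SD) | MAR-imputation bias (SD) |
|---|---|---|
| Unobserved outcome | 0.083 | 0.065 |
| Observed baseline (MAR true) | 0.043 | 0.003 |

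In the first row the two methods differ by only 0.018 SD and both are wrong. In the second they differ by 0.040 SD although imputation is right. The gap is larger when MAR holds than when it fails. With 10% dropout in both arms and the same mechanism, the bias in the between-arm difference is about zero for both methods. The problem needs some imbalance between arms.

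**4. How many households could complete-case analysis keep?** If a complete case means every survey present, and surveys are missed independently at rate q per month (assumed), the share kept is (1 − q)^m.

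| q | All 24 kept | Of 80 | All 12 kept |
|---|---|---|---|
| 0.5% | 89% | 71 | 94% |
| 1% | 79% | 63 | 89% |
| 2% | 62% | 49 | 79% |
| 5% | 29% | 23 | 54% |
| 10% | 8% | 6 | 28% |

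The rate at which half are lost:

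- m = 24: 1 − 0.5^(1/24) = 2.85%; on top of the planned 10% dropout, 1 − (0.5/0.9)^(1/24) = 2.42%
- m = 12: 5.6% and 4.8% by the same formulas

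With the stated 10% dropout and no intermittent misses, 90% stay complete: 88 × 0.9 ≈ 79 households.

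Under the step 1 formula, 40 complete households would have power 0.42 at f = 0.10, and 24 would have 0.22.

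**5. Size of a departure from MAR.** If a fraction d of an arm has left and truly scores k ACT points worse than imputed, that arm's mean is overstated by d × k. The between-arm bias is d_active × k_active − d_sham × k_sham. With assumed d = 10%, k = 3 in the active arm and no departure in sham, it is 0.3 points; with d = 20%, 0.6 points. Equal departures in both arms cancel. Averaged over the 12 post-intervention months, only the months after withdrawal contribute, so the figure is smaller.

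**The case against.** **This is detail for the analysis plan.** The article is a condensed account, the plan is still to be finalised, and an analysis under a not-at-random assumption is typical plan content. This stands in part: the article does not say its list is exhaustive, so nobody can conclude that informative withdrawal will go unexamined. But the article does state a check, and that check does not do the job. That is a choice open to comment, not merely an absence.

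**Complete case may mean something else.** The comparison is named in the same sentence as the mixed models. A mixed model without imputation drops missing months, not households, and is valid under MAR. On that reading the stronger-assumption argument and the household-loss figures both fall away. The main point survives, because two MAR-based analyses cannot test MAR.

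**Complete-case analysis would discard most households.** A reader might infer this from 24 monthly surveys, but the documents do not support it. They give no missed-survey rate, the only attrition figure is 10%, and the pre-intervention period may be shorter than a year. Misses that cluster within households leave more complete cases than the formula gives.

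**The active effect would be overstated.** A reader might infer this too, but the direction is not established. Sham units are designed to match in airflow, noise or appearance, so leaving for those reasons should be similar across arms. Leaving for lack of benefit could be commoner under sham, which would reverse the sign.

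**The comparison is not worthless.** It shows how much the result depends on the imputation model. That is true, but it is a different question.

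**Conclusion.** The point holds in a limited form. Of the analyses stated in the article, none examines departures from MAR, and the one offered as the missing-data sensitivity analysis cannot do so under either reading of complete case. Agreement between its two results would not support MAR, and disagreement would not show that MAR fails.

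The logic needs no numerical assumption. The sizes do: 0.08 against 0.07 SD comes from an assumed mechanism with unequal dropout, and 0.3 to 0.6 ACT points from assumed, one-sided departures. The loss of more than half of households is a possibility that begins at roughly 2.4% to 2.9% of monthly surveys missed, given independent misses and all 24 surveys required. It is not a forecast. No stated sample size or power figure changes.

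**What to change.** In the Data management and statistical analysis plan section, add a delta-adjusted multiple-imputation tipping-point analysis for ACT on all randomised households:

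- Shift the values imputed after withdrawal by delta, varied separately in the active and sham arms, for example 0 to 4 ACT points worse.
- For each active-versus-sham comparison, report the combinations of deltas at which the conclusion changes.
- Define complete case and label those results descriptive. A likelihood mixed model on observed months is a better companion analysis, but it is still MAR-based and does not replace the delta analysis.
- Imputing active-arm leavers from the matching sham arm is optional. It needs new imputations and presumes that benefit ends when surveys end, whereas the devices may keep running.

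The cost is a little extra imputation work and no new data. The result may look less robust. Data collection had not begun at the time of writing and the plan is to be finalised before unblinding, so this can still be prespecified.

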Moreover, the study will involve mold assessments through spore-trap analysis of air samples, direct microscopic examination of surface samples, and fungal DNA sequencing of dust samples. Indoor and outdoor air samples will be collected using an Air-O-Cell sampling cassette with a calibrated Bio-Pump (Environmental Express), surface samples with sterile cotton-tipped swabs, and dust samples from HVAC filters and/or damp areas with visible mold or water damage (e.g., kitchen and bathroom) in each home at V1 and V4. Air and surface samples will be submitted to the accredited laboratory Eurofins USA for spore-trap and direct microscopic analyses. The dust samples will be sent to Co-PI [name]’s lab for storage, DNA extraction, followed by fungal Internal Transcribed Spacer (ITS) sequencing at the North Texas Genome Center at UTA within three months of sample collection completion.

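### The primary repeated-measures ANOVA does not adjust ACQ, lung function or mold for their own pre-intervention values, which costs some power; the amount depends on an unstated correlation

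*Protocol article*

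**What the plan says.** In the protocol article, the section on data management and statistical analysis gives one primary method for air quality, mold and asthma-related outcomes: effects are evaluated "by comparing the intervention and control (sham) groups using repeated measures analysis of variance (ANOVA) with a within-between interaction". Pairwise comparisons follow for Group 1 vs 2, 3 vs 4 and 1 vs 3, with Tukey's adjustment. Monthly ACT scores are given a mixed-effects model.

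The outcomes at issue are those collected at home visits:

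- ACQ, listed under primary outcome measures: "we will administer the ACQ during the home visits (V1-V4) to assess asthma control more comprehensively".
- PFT, at the same four visits. Study design splits these visits as "two during the pre-intervention period and two during the post-intervention period".
- Mold, sampled "in each home at V1 and V4", so once before and once after the intervention.

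Table 1 sizes the trial on the same model and counts the pre-intervention values among the repeated outcomes: "Pulmonary Function Testing (No. of measurements = 4" and "Mold Measurements (No. of measurements = 2, baseline & end-line". Its footnote confirms the method: "Sample sizes were calculated based on repeated measures ANOVA (α = 0.05, power = 0.80".

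Baseline information appears elsewhere only as a stratification factor (baseline health status, under Interventions) and as subgroup variables (baseline severity and baseline air quality). No section enters an outcome's own pre-intervention value as a covariate.

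**The concern.** A comparison of raw change fixes the slope of the post-intervention value on the baseline at 1. Under randomisation the two arms of a contrast have the same expected baseline. A model that estimates the slope therefore targets the same effect, with smaller variance whenever the pre-post correlation is below 1. The trial already collects these baselines, so the gain needs no new data.

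With about 20 homes per arm, precision is scarce. The outcomes with few measurements lose most. They include ACQ, a listed primary outcome, and mold, which is part of the primary objective. A chance baseline difference in so small an arm also passes into raw change through regression to the mean.

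**Working it through.** **Inputs.** Four arms, α = 0.05, and the effect sizes f and totals N of Table 1. Measurements m = 2 (mold) and m = 4 (PFT; ACQ has the same layout but no row of its own). About 20 homes per arm, assumed from 40 ERV and 40 air cleaner homes split equally. The correlation ρ is not stated. Compound symmetry and one analysed unit per home are assumed.

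**Step 1: reproduce Table 1.** Noncentral F with λ = N·m·f²/(1−ρ), df1 = 3(m−1), df2 = (N−4)(m−1).

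- Mold, f = 0.20, N = 76, ρ = 0.5: λ = 76 × 2 × 0.04 / 0.5 = 12.16, power 0.823 (stated 0.82).
- Mold, f = 0.10, N = 280: λ = 11.2, power 0.806 (stated 0.81).
- PFT, f = 0.10, N = 200: λ = 16, df1 = 9, power 0.804 (stated 0.80).

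All 14 PFT and mold powers reproduce to rounding at ρ = 0.5. At ρ = 0.3 or 0.7 they do not (mold, N = 280: 0.65 or 0.96). Table 1 therefore rests on ρ = 0.5.

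**Step 2: variance ratio.** With k measurements before and k after, the baseline-adjusted variance divided by the raw-change variance is

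(1 + (2k−1)ρ) / (2(1 + (k−1)ρ)).

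For mold (k = 1) this is (1+ρ)/2, which is 0.75 at ρ = 0.5. For ACQ and PFT (k = 2) it is (1+3ρ)/(2(1+ρ)) = 2.5/3 = 0.833.

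**Step 3: power of one pairwise contrast.** Start where raw change has 80% power (two-sided 5%). After adjustment, power = Φ((1.960 + 0.842)/√ratio − 1.960). For mold at ρ = 0.5: 2.802/0.866 − 1.960 = 1.275, giving 89.9%. For four visits: 2.802/0.913 − 1.960 = 1.109, giving 86.6%.

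| ρ | Mold ratio | Mold power | ACQ/PFT ratio | ACQ/PFT power |
|---|---|---|---|---|
| 0.3 | 0.65 | 93.5% | 0.731 | 90.6% |
| 0.5 | 0.75 | 89.9% | 0.833 | 86.6% |
| 0.7 | 0.85 | 86.0% | 0.912 | 83.5% |
| 0.8 | 0.90 | 84.0% | 0.944 | 82.2% |

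**Step 4: cost of estimating the slope.** Simulation with 20,000 replicates, 20 per arm and ρ = 0.5 gives variance ratios of 0.77 (mold) and 0.86 (four visits), with the same mean effect from both estimators. Simulated power goes from 0.801 to 0.893 for mold and from 0.802 to 0.858 for four visits, so about 9 and 6 points. The table above is before this cost, which takes off about one point at ρ = 0.5.

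**Step 5: monthly ACT.** With 12 values before and 12 after, the ratio is 0.92, 0.96 and 0.98 at ρ = 0.3, 0.5 and 0.7, a gain of about 1 to 3 points. The simulated ratio at ρ = 0.5 is 0.98.

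**The case against.** **The size is uncertain.** A reader might infer a fixed loss of 7 to 10 points. The documents do not support that. The value ρ = 0.5 shows what was entered in the power program, not how ACQ, FEV1 or mold counts correlate over time. FEV1 and FVC are recorded from age 5 to adulthood with no percent-predicted scaling stated, so their within-person correlation could plausibly be high (an assumption). The 80% starting point is also a choice. With a true difference of 0.8 SD at 20 per arm and ρ = 0.5, the four-visit contrast already has 0.936 power, and adjustment raises it only to 0.968. These objections stand.

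**The four-visit test is not a raw-change test.** The stated interaction has (4−1)(4−1) = 9 degrees of freedom and covers all visit contrasts. Only for mold is the whole interaction the raw-change comparison. For ACQ and PFT the point concerns the pre-to-post contrast within it. This stands too.

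**Baselines need not agree across all four arms.** Under Interventions, homes that cannot take an ERV enter only the air cleaner arms. A reader might work out a power gain for the four-arm omnibus test, or constrain one baseline mean across all arms. Neither has a basis here. Equal expected baselines hold for Group 1 vs 2, and for Group 3 vs 4 if the active-to-sham ratio is the same for both kinds of home.

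**Stratification helps already.** Stratifying on baseline health status limits chance imbalance in the asthma measures, so the regression-to-the-mean worry is partly met. The simulation did not include stratification.

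**The pairwise figures use an unadjusted 5% test.** Tukey's critical value does not shrink the gain: starting again from 80%, the formula gives 91.4% (mold) and 87.8% (ACQ/PFT) at ρ = 0.5.

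**The article may leave covariates to the full plan, and it mentions mixed models.** The article nonetheless names the primary method and sizes the trial on it, so this is a stated choice. The general mixed-model sentence sits in the missing-data paragraph. It names neither a baseline covariate nor a common baseline mean, and a mixed model with free group-by-time means is no more efficient on this point.

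**Conclusion.** The point holds as a matter of efficiency. At 20 homes per arm and ρ = 0.5, a pairwise contrast with 80% power on raw change would gain about 9 points for mold and about 6 for ACQ and PFT from baseline adjustment. At ρ = 0.7 to 0.8 the gain is about 4 to 6 points for mold and 2 to 4 for ACQ and PFT; at lower correlation it is larger. For monthly ACT it is negligible, so the point does not rest on ACT.

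These sizes assume compound symmetry, equal allocation and one analysed unit per home. A reader might infer that the planned analysis is biased. It is not: under randomisation both estimators are unbiased on average. The change is worth making because it is nearly free, not because the planned analysis is invalid.

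**What to change.** In the data management and statistical analysis section, specify ANCOVA or a linear mixed model for ACQ, PFT and mold:

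- **Response:** the post-intervention values (V3 and V4; V4 only for mold).
- **Factor:** treatment arm.
- **Covariate:** the outcome's own pre-intervention value (mean of V1 and V2; V1 for mold).
- **Contrasts:** Group 1 vs 2 and Group 3 vs 4; Group 1 vs 3 only among homes that were eligible for either device.
- **Common-baseline models:** if one is preferred, impose the constraint only within a randomised contrast or within the ERV-eligible stratum, never across all four arms.
- **Sensitivity analysis:** keep the raw-change repeated-measures ANOVA.

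The cost is wording and one degree of freedom per outcome, with no new visits, homes or data. The timing allows it: the article says that data collection has not begun and that the analysis plan will be finalised before data lock.
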